**Study process (Flow diagram)**

>33 Slum areas in Pokhara Metropolitan

2 slum areas will be purposively selected

One slum area will be conveniently chosen for control group

One slum area will be conveniently chosen for intervention group

Eligible women of 30-60 years will be completely enrolled (n=155)

Eligible women of 30-60 years will be completely enrolled (n=155)

Baseline data collection

CIC-led Intervention

CHW-led Intervention

1st Follow up, data collection (3^rd^ week)

2^nd^ Follow up, data collection (6^th^ week)

**Figure 1: Study process (flow diagram)**

**Sample size calculation**

The sample size was calculated using screening rate at baseline study=73% (p1), the expected change in proportion up to 87% (p2), ^[13]^ with other values conventionally, as Z_a/2_=1.96 (for 95% CL), Z_β_=0.84 (β=80%), and using the formula for sample size (n)=[(Z_a/2_+ Z_β_)^2^. (p1(1-p1)+p2 (1-p2))]/(p1-p2)^2, we obtained 124.08 for each group. With an attrition rate of 20%, the final sample size for each group will be 155.

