**Abstract**

**Introduction**
Cervical cancer is a major public health issue in Nepal, particularly among women in low-resource settings like urban slums. Despite national screening guidelines, uptake remains low due to limited awareness, access barriers, and sociocultural factors. Community-based health education may help improve screening behavior.

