**Introduction**

Cervical cancer ranks as one of the most prevalent cancers among women worldwide.^[1]^ The majority of cervical cancer-related deaths occur in low- and middle-income countries. ^[1]^ The incidence and mortality rates of cervical cancer vary among the World Health Organization’s (WHO) regions.^[1–3]^ The disparities across regions are attributed to inequalities in access to resources for prevention, screening, and treatment of cervical cancer, as well as social and economic factors such as poverty and gender biases. ^[1,4]^ Cervical cancer predominantly affects younger women, with 20% of children losing their mothers to this disease. ^[5]^

In 2020, cervical cancer was the leading cancer diagnosed among Nepalese women, resulting in the highest number of cancer-related deaths.^[6]^ The age-standardized incidence rate stood at 16.4 cases per 100,000 women, with 2,244 new diagnoses and 1,493 fatalities. ^[6]^ According to the national cervical cancer screening and prevention guidelines, women aged 30-60 are advised to undergo visual inspection with acetic acid (VIA) screening every five years, which initially targeted screening at least 50% of women aged 30 to 60 years, which was later revised to 70% in 2020. ^[7]^ However, by 2019, only 8.2% of women aged between 30 and 49 had undergone cervical screening in Nepal.^[8]^ Several obstacles, including limited awareness, limited trained healthcare professionals, and feelings of embarrassment, hinder the utilization of cervical cancer screening.^[9,10]^ On the other hand, factors like the gender of healthcare providers, effective counseling, and the privacy of screening services are frequently cited as facilitators for screening. ^[8]^

Community Information Channel-led interventions using posters are provided by the health facilities to aware women of cervical cancer. ^[7]^ According to the 2^nd^ amendment of the National Female Community Health Volunteer (FCHV) Program Strategy in 2076 BS, FCHV must have at least passed the SLC. ^[11]^ The fragmented nature of health programs poses a challenge for Female Community Health Volunteers to coordinate activities and deliver the results.^[12]^ So, an assessment of an integrated community health worker (CHW) program model is needed to support the implementation of community-based health interventions for the prevention and control of cervical cancer effectively.

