**Intervention**

Ten participants who had at least passed the SLC will be enrolled as community health workers (CHWs) in the intervention group. Training on cervical cancer will be provided to the CHWs by the principal investigator and a nurse using presentation slides. The training will be for one day (4 hours). CHWs will be mobilized in the intervention group using flip charts and brochures. After a day of receiving the training, CHWs will reach the doors of the participants to provide health education on cervical cancer, which will be monitored once by the principal investigator. CHWS will visit the participants just once for an education session, which will take 15 minutes for each participant. CHWs will distribute brochures to every participant in the intervention group. All of the participants of the intervention group will receive the intervention. In the control group, posters will be displayed in two different locations after the baseline study.

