**Data Analysis**

Statistical Package for Social Sciences (SPSS v22) will be used to store and analyze quantitative data. A descriptive analysis will be performed, where medians and interquartile range (IQR) will be used to characterize continuous variables, while frequencies and percentages will be used to summarize categorical data. P-values will be calculated, and less than 0.05 will be deemed statistically significant in all two-sided analyses, where needed, using the Pearson's chi-squared test, Mann-Whitney test, Wilcoxon test, and Mc. Nemar test. Effect size (r) in the Mann-Whitney and Wilcoxon tests will be calculated using the formula r=|Z|/√n ^[14]^. The intervals for small effect, intermediate effect, and strong effect are 0.1 to 0.3, 0.3 to 0.5, and 0.5 and higher, respectively ^[15]^. No interim analysis will be performed because of the short time duration.

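### The only power statement rests on 73% rising to 87% screened, which conflicts with the protocol's own background and uses a before-after change as the between-group difference

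*Protocol*

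**What the plan says.** Protocol, Sample size calculation: "The sample size was calculated using screening rate at baseline study=73% (p1), the expected change in proportion up to 87% (p2". Both values carry one citation, to a community-based screening intervention study. They go into the unpooled formula for two independent proportions with "Z_a/2_=1.96 (for 95% CL" and 0.84 for 80% power. The result is 124.08 per group, raised to 155 for 20% attrition. This is the only sample size calculation in the document.

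Protocol, Introduction: "by 2019, only 8.2% of women aged between 30 and 49 had undergone cervical screening in Nepal". The Abstract, writing of low-resource settings such as urban slums, says that "uptake remains low due to limited awareness, access barriers, and sociocultural factors".

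Protocol, Intervention: "In the control group, posters will be displayed in two different locations after the baseline study". The comparator is therefore an active information channel, and both groups are measured at baseline, week 3 and week 6.

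Protocol, Outcomes: change in knowledge is primary; change in screening uptake is listed as secondary.

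**The concern.** Two things do not fit.

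First, the planning rate of 73% is about nine times the only Nepalese figure that the protocol gives (73/8.2 = 8.9). The case for the study is that few women are screened, yet the calculation starts from a population in which nearly three quarters already are. No sentence reconciles the two. At 73%, the planned gain would also mean that 14 of every 27 unscreened women (52%) are screened by week 6 after one 15-minute visit. That is a consequence of the 73%, not a separate fault.

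Second, by their own labels p1 is a baseline rate and p2 is that rate after change. The formula compares two groups at one time. It describes CHW education against posters only if the poster group is still at p1 at follow-up. The protocol gives no expected follow-up rate for the poster group, and its Discussion expects the health education interventions to raise participation in screening.

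What is at stake is how an uptake result is read. A null result from a study reported as having 80% power would be taken as evidence against CHW education, although that power belongs to a scenario that the document does not support.

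**Working it through.** **Inputs from the protocol.** p1 = 0.73, p2 = 0.87, z = 1.96 and 0.84, attrition 20% (Sample size calculation); national rate 0.082 (Introduction). Two-sided testing is confirmed in Data Analysis: "less than 0.05 will be deemed statistically significant in all two-sided analyses".

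**Assumed, not in the protocol.** Every poster-group follow-up rate other than 73%, and every gain other than 14 points.

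**1. The protocol's own figure.**
n = (1.96 + 0.84)² × (0.73×0.27 + 0.87×0.13) / 0.14² = 7.84 × (0.1971 + 0.1131) / 0.0196 = 124.08. Then 124.08/0.8 = 155.1, stated as 155. Both figures reproduce.

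**2. Power with 124 evaluable women per group**, from the same formula turned round:
power = Φ(|p1 − p2| / √[(p1(1−p1) + p2(1−p2))/124] − 1.96).

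For 73% vs 87%: √(0.3102/124) = 0.0500; 0.14/0.0500 = 2.799; Φ(0.839) = 79.9%.

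**3. The poster group also moves (CHW group held at 87%).**

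| Poster group at week 6 (assumed) | Standard error | Difference / SE | Power | n per group for 80% |
|---|---|---|---|---|
| 73% | 0.0500 | 2.799 | 80% | 124 |
| 75% | 0.0492 | 2.437 | 68% | 164 |
| 77% | 0.0484 | 2.067 | 54% | 228 |

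**4. Start from the protocol's national figure instead (8.2% as an illustrative poster-group rate).**

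| CHW group at week 6 | Gain (assumed) | Power |
|---|---|---|
| 13.2% | +5 points | 25% |
| 16.2% | +8 points | 49% |
| 18.2% | +10 points | 65% |
| 22.2% | +14 points | 88% |

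With the protocol's own 14-point gain, power is higher than stated, and (1.96 + 0.84)² × (0.082×0.918 + 0.222×0.778)/0.14² gives 99.2 women per group before attrition. With smaller gains it is lower. The direction depends on inputs that the protocol does not supply.

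**5. Difference detectable at 80% power with 124 per group**, solving the formula for p2:

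| Poster group at week 6 (assumed) | CHW group needed | Difference |
|---|---|---|
| 8.2% | about 20.5% | 12.3 points |
| 10% | about 23% | 13 points |
| 15% | about 29.6% | 14.6 points |
| 20% | about 35.7% | 15.7 points |

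**6. Why one replacement pair would not do.** Suppose 8.2% vs 20.5% were written in. If the poster group then reached 10.2% against the same 20.5%, power would be 62%; at 12.2% it would be 43%. That would again use a pre-intervention rate as the control rate.

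All figures use the protocol's formula and treat women as independent.

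**The case against.** The strongest reply has four parts.

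- **The 8.2% is not the slum rate.** It is national, for ages 30-49, by 2019. The trial enrols ages 30-60 in two slum areas matched on distance to screening services. This stands. The figure shows that 73% is unsupported and at odds with the background; it does not give the true rate.
- **Using the baseline rate as the expected control rate is a common simplification**, and the control is only posters in two places. This stands in part. The calculation is valid if poster-group uptake stays at 73%, but the protocol does not state that assumption, and its use of an information channel as comparator does not support it. The 75% and 77% are illustrations, not predictions.
- **The effect on the trial is limited.** A reader might infer that the trial is too small. The documents do not support that: the same 14-point gain from 8.2% would have 88% power, and the lower powers come from gains assumed here.
- **Uptake is secondary.** This stands. A reader might infer that the power of the main comparison is wrong. The calculation does not address the primary outcome of knowledge, so nothing follows from it for that outcome in either direction.

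It would also go too far to say that 80% power is false for this population. The true rates are unknown, so the figure is unestablished rather than disproved.

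**Conclusion.** The concern holds in this limited form. The protocol's only power statement uses rates that conflict with its own background, and it describes the CHW-versus-poster contrast only under an unstated assumption of no change in the poster group. The claim of 80% power is therefore not established for this population or this contrast.

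On size: if the CHW group reaches 87%, a rise of 2 or 4 points in the poster group takes power from 80% to 68% or 54%. At a poster-group rate of 8.2%, power runs from 25% to 88% for gains of 5 to 14 points. These figures rest on 124 evaluable women per group, the protocol's formula and the assumed rates shown.

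The error can run either way and concerns a secondary outcome, and the remedy leaves enrolment and analysis as they are. It should be corrected, but it ranks below a must-fix.

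**What to change.** Keep 155 per group and rewrite the Sample size calculation paragraph:

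- Define p1 and p2 as the expected week-6 screening proportions in the poster and CHW groups, and drop 73% and 87% as the basis.
- Replace the single 80% statement with the differences detectable at 80% power with 124 evaluable women per group, over a range of assumed poster-group rates: about 8.2% vs 20.5%, 10% vs 23%, 15% vs 29.6% and 20% vs 35.7%. Say that 8.2% is one point in the range, not the known control rate.
- Show power for smaller gains as well: from 8.2%, about 25% for +5, 49% for +8 and 65% for +10 points.
- State that the figures apply to the secondary outcome of screening uptake and not to the primary outcome of knowledge.

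The cost is one reworded paragraph and a less favourable stated figure. No extra participants are needed, and the conduct and analysis of the trial do not change.

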**Data collection**

Data will be collected by trained female data enumerators from a public health background through face-to-face interviews using a structured questionnaire adapted from relevant literature and previous studies on similar topics. The questionnaire covers the basic information of the study subjects, such as age, marital status, education level, and occupation. A total of 14 questions (36 scores) will be asked to assess knowledge about cervical cancer disease itself and its risk factors, and prevention and control measures. Behavior related to cervical cancer screening will be assessed by the utilization of a cervical cancer screening question. Pre-testing of the study tool will be done among 31 women aged 30 to 60 years in a slum area within Ward 29 of Pokhara Metropolitan to ensure its reliability and validity.

A baseline study will be conducted in the selected slum areas to assess the knowledge of cervical cancer and demographic and behavioral characteristics of the participants. Post-test will be done among both the study groups (intervention and control) after the third week and the sixth week.

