**Study participants and sampling procedure**

Women aged 30-60 years from two slum areas of Pokhara Metropolitan City will be recruited as study participants. In the first stage, two slum areas of the Pokhara Metropolitan City will be selected purposively to ensure maximum matching between both slum areas, to ensure participants from both the control and intervention groups share similar characteristics. To control the potential confounding effect of accessibility on screening uptake, slum areas with similar distances to health facilities with VIA services will be selected. In the second stage, one slum area will be conveniently selected as the intervention group, and the other one will be conveniently designated as the control group. In the third stage, the list of women aged 30-60 years in both the selected slum areas will be prepared with the help of the head of the slum areas, and the participants will be randomly enrolled in the study.

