**Outcomes**

The primary outcome will be a change in knowledge of cervical cancer. Secondary outcomes include changes in cervical cancer screening uptake, perceived susceptibility, perceived severity, and behavioral intention related to cervical cancer from baseline to midterm and endline assessments.

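### Screening uptake rests on one face-to-face question with no stated date, evidence of testing or masking, so over-reporting after the home visit could inflate the intervention arm

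*Protocol*

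**What the plan says.** Three parts of the protocol bear on this point.

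- **Measurement.** Under Data collection, "Behavior related to cervical cancer screening will be assessed by the utilization of a cervical cancer screening question". The mode is an open interview: "Data will be collected by trained female data enumerators from a public health background through face-to-face interviews using a structured questionnaire". The interview takes place at baseline, after week 3 and after week 6. The only quality step named is a pre-test of the tool in 31 women.
- **Contrast between arms.** Allocation is by whole slum: "one slum area will be conveniently selected as the intervention group, and the other one will be conveniently designated as the control group". In the intervention slum, "CHWS will visit the participants just once for an education session, which will take 15 minutes for each participant", and each woman also receives a brochure. For the comparison slum, "In the control group, posters will be displayed in two different locations after the baseline study".
- **Role of the outcome.** Knowledge is primary. "Secondary outcomes include changes in cervical cancer screening uptake, perceived susceptibility, perceived severity, and behavioral intention" are listed next. Screening behavior is nevertheless in the title, and the Sample size calculation uses screening proportions of 73% and 87%.

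The Introduction adds that "women aged 30-60 are advised to undergo visual inspection with acetic acid (VIA) screening every five years", so many years of past testing could lie behind a positive answer.

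**The concern.** A self-reported answer is a weak measure when one arm has just been taught, at home and in person, that screening is expected. Two errors are plausible. A woman may say she was tested because that is the approved answer. Or, having learned what screening is, she may now count an earlier pelvic examination as screening. Either turns a baseline no into a later yes without a new test. Control women see only posters, so these errors are likely to be less common there.

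The difference in uptake would then mix real screening with differential reporting, and chi-squared and McNemar tests cannot separate the two. At stake is the claim that education by community health workers raises screening. How an outcome is ascertained is protocol content, so the point does not depend on an unseen analysis plan.

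**Working it through.** **1. The plan's own figure.** Using the protocol's formula with p1 = 0.73 and p2 = 0.87:

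(1.96 + 0.84)² × (0.73 × 0.27 + 0.87 × 0.13) / 0.14² = 7.84 × 0.3102 / 0.0196 = 124.08 per group.

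124.08 / 0.8 = 155.1, stated as 155. The figure reproduces. Conversely, 155 × 0.8 = 124 women per arm remain for analysis.

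**2. Inputs for the bias check.**

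- Baseline screening b: 8.2% (the national figure for ages 30-49 in the Introduction), 73% (the planning value), and 30% as an assumed middle value.
- True new uptake c among unscreened women: 3% or 5%, the same in both arms (assumption).
- False yes answers f among intervention women still unscreened: 10% (assumption). None in the control arm.

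The protocol gives no value for c or f.

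**3. Formulas.**

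- Control: P_C = b + (1 − b)c
- Intervention: P_I = b + (1 − b)[c + (1 − c)f]
- Spurious difference: (1 − b)(1 − c)f

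Example with b = 0.082, c = 0.03, f = 0.10: P_C = 0.082 + 0.918 × 0.03 = 0.110; P_I = 0.082 + 0.918 × 0.127 = 0.199; difference 0.918 × 0.97 × 0.10 = 0.089, or 8.9 points.

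**4. False-positive rate** of the two-sided 5% chi-squared test (pooled z, no continuity correction), by exact binomial calculation. The two values in each range are for c = 5% and c = 3%.

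| Baseline b | Spurious difference, all women (points) | All 124 per arm | Only women unscreened at baseline (n per arm) |
|---|---|---|---|
| 8.2% | 8.7-8.9 | 46-50% | 71-82% (114) |
| 30% | 6.7-6.8 | 19-20% | 58-69% (87) |
| 73% | 2.6 | 8% | 27-32% (33) |

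The subset sizes are 124 × 0.918, 124 × 0.70 and 124 × 0.27, rounded.

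**5. Range over f.** Here all 124 women per arm are tested, uptake is identical in both arms, c = 0, and the normal approximation is used.

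- b = 8.2%: f = 5%, 10%, 15% gives 21.8%, 58.2%, 86.2%.
- b = 73%: f = 10%, 20%, 30% gives 7.7%, 16.7%, 32.8%.

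To imitate the full 14-point planned effect, f must be 0.14 / 0.918 = 15.3% at the low baseline and 0.14 / 0.27 = 51.9% at the planning baseline.

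**6. The paired test.** For McNemar within the intervention arm, six changes from no to yes with none in reverse give an exact p of 2 × 0.5⁶ = 0.031, whatever the baseline. Six mistaken answers would be enough.

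**The case against.** The strongest reply is that the plan already places screening in time. The same question is asked at baseline, the outcome is change, and McNemar is paired, so a woman who truthfully answers no and then yes was screened in between. That stands for truthful answers; it does nothing for false or re-labelled ones. A date given in interview is also self-report, which is why the card matters more than the date.

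Several stronger readings are tempting, and the protocol does not support them.

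- *The question is undated.* The questionnaire is not shown. A date or recall window may exist; it is only unreported.
- *Interviewers know which slum was taught.* Arm equals slum and no masking is stated, so a reader might infer this. The protocol does not say what enumerators are told or how they are assigned, and nothing says that those who teach also interview.
- *The bias can only run upward, in one arm only.* Posters and repeated interviews could also move control answers. Education might teach some women that an earlier examination was not screening. Mainly upward in the intervention arm is a fair expectation, not a certainty.
- *The error rate is 71-82%.* That needs an analysis restricted to women unscreened at baseline, which the Data Analysis section does not state.

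It is also fair to say that self-report is an ordinary choice in a small community survey.

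**Conclusion.** The concern holds as a weakness in the stated measurement, worth correcting before follow-up begins. As written, the plan leaves the uptake comparison open to differential over-reporting, and pre-testing the tool does not check answers against any evidence.

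Its size cannot be fixed from the protocol. Under the 10% assumption and an analysis of all women, the effect ranges from serious if baseline screening is near the national 8.2% to slight if it is near the planning value of 73%. These figures assume independent women, no other difference between the slums and no over-reporting in the control arm; over-reporting in that arm would shrink them.

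A reader might take the point to undermine the trial as a whole. It does not: the primary outcome, knowledge, is untouched, and no change in sample size follows.

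**What to change.** In Data collection, with a matching line in Outcomes:

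1. Define new uptake as a cervical screening test dated after the baseline interview.
2. At weeks 3 and 6, ask every woman who reports screening, in both slums, for the date and the facility, and ask to see her card or slip.
3. Report card-seen and self-report-only uptake separately by arm.
4. Assign enumerators across both slums where feasible, so that interviewer habits do not coincide with arm.

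If the questionnaire already asks for these details, saying so in the protocol settles most of the point.

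The cost is a few extra questions for women who report a test and some attention to the enumerator roster. The downside is that some women will have no card, so the card-confirmed rate will lie below the self-reported rate; showing both lets the reader see the gap in each arm. A check against facility registers would be stronger, but it needs access and record matching, so it is not part of this low-cost change.
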